### Follow-up and points of data capture

The points of data capture in the trial are as follows: Intervention period (24 weeks): Baseline, medication for 4 weeks ± 2 days, medication for 12 weeks ± 3 days, medication for 24 weeks ± 5 days for hospital visits, and telephone follow-up for 36 weeks ± 7 days after enrolment.

The corresponding items will be measured according to the time point of data collection. The detailed information is shown in Fig. 2.

**Fig. 2 Fig2:**
[figure not shown]
Study schedule (Standard Protocol Items: Recommendations for Interventional Trials, SPIRIT). Abbreviations: SJP, Suxiao Jiuxin Pill; CCS, Canadian Cardiovascular Society; TCM, Traditional Chinese medicine; SAQ, Seattle angina questionnaire; EKG, electrocardiogram; MACE, major adverse cardiac events

### Sample size

The sample size will be calculated based on a 10% increase in effective treatment after treatment. It was hypothesized that the effective treatment rate for patients receiving standard western medicine treatment is 83% and that for patients receiving both traditional Chinese medicine and western medicine treatment is 93%. The participants will be arranged into the treatment or control group in a ratio of 1:1. According to the one-tailed difference test formula, there should be 162 participants in each group (significance level α is 0.05 and power (1-β) is 0.80 in the one-sided test) and the incomplete rate should be less than 20%. A total of 324 participants will be included.

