### Statistical approach

Efficacy will be determined by the full analysis set (FAS) and per protocol set (PPS), while the safety assessment will be based on the safety set (SS). The statistical evaluation of FAS will follow the principle of intention to treat (ITT). For the missing values of the main efficacy evaluation indicators, the method of the last observation carried forward (LOCF) will be used. Continuous variables were shown as mean ± standard deviation (SD) and were compared using the *t* test or the nonpara-metric Mann-Whitney *U* test, as appropriate. The count variables were shown as the number of cases and percentage, and the chi-square test was used for comparative analysis. The symptom improvement rate of angina is to calculate the total score of angina pectoris according to the degree of pain, the number of attacks, and the duration. The total score is effective when it is lower than or equal to 30% of the baseline, and invalid when it is less than 30%. The symptom improvement rate of angina was analyzed by chi-square test. The participants who had any cardiovascular event during 24 weeks of treatment will be identified as the occurrence of cardiovascular events. The RR and 95% confidence interval of the two groups were calculated by logistic regression model. Statistical analysis will be performed using SAS 9.4 software.

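### The 80% power is for a one-sided 5% test, but the angina response is to be analysed by a chi-square test with no one-sided level stated; read as two-sided 5%, power is about 70% to 79% depending on loss

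*Protocol article*

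**What the plan says.** The Sample size section of the protocol article compares response rates of 83% (standard treatment) and 93% (standard treatment plus SJP) with 1:1 allocation. Using a one-tailed formula, it states that "there should be 162 participants in each group (significance level α is 0.05 and power (1-β) is 0.80 in the one-sided test"). The same sentence says that incomplete cases should be below 20%, and the total is 324.

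The Statistical approach section turns to the same endpoint: "The symptom improvement rate of angina was analyzed by chi-square test". It gives no significance level, does not say whether the test is one- or two-sided, and names no directional form of the test. It analyses efficacy in both the full analysis set (FAS), following intention to treat, and the per protocol set (PPS). Missing values of the main efficacy measures are filled by last observation carried forward (LOCF).

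The Abstract lists symptom improvement from baseline to 4 weeks as a primary outcome, together with MACE.

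**The concern.** A power figure belongs to a particular test at a particular level. Here the level and direction appear only in the sample-size paragraph, and the analysis paragraph names a test whose usual p-value ignores direction, because the chi-square statistic squares the difference. A reader who takes the two sections together cannot tell which rule decides success.

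The choice matters in a definable zone. In favour of SJP, the one-sided 5% rule succeeds when z is at least 1.645 (chi-square at least 1.645² = 2.71). The two-sided 5% rule needs z of at least 1.960 (chi-square at least 1.960² = 3.84). A chi-square p-value between 0.05 and 0.10 in SJP's favour is therefore a success under one rule and a failure under the other. If the rule is not fixed before unblinding, it could be chosen after the result is known. The two rules also carry different false-positive rates for a benefit claim: 5% and 2.5%.

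**Working it through.** **Inputs (Sample size section):** p1 = 0.83, p2 = 0.93, difference d = 0.10, mean rate 0.88, one-sided α = 0.05 (z = 1.645), power 0.80 (z = 0.842), loss ceiling 20%, 162 per arm. The two-sided 5% critical value is z = 1.960.

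**Formula (pooled variance under the null, no continuity correction):**

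n per arm = [z_α √(2 × 0.88 × 0.12) + z_β √(0.83 × 0.17 + 0.93 × 0.07)]² / d²

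The roots are √0.2112 = 0.4596 and √0.2062 = 0.4541.

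**1. Reproducing the plan's figure (one-sided 0.05)**

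- n = (1.645 × 0.4596 + 0.842 × 0.4541)² / 0.01 = 129.5 evaluable per arm.
- With 20% loss: 129.5 / 0.8 = 161.9, hence 162. (Rounding up to 130 first would give 163.)

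So 162 is the one-sided size with the 20% loss already included.

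**2. The same formula, two-sided 0.05**

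- n = (1.960 × 0.4596 + 0.842 × 0.4541)² / 0.01 = 164.6, that is 165 evaluable per arm.
- With 20% loss: 164.6 / 0.8 = 205.7, that is 206 per arm (207 if 165 is inflated).

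**3. Power at the planned size**

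Power = Φ[(d√n − z_α × 0.4596) / 0.4541], with n = 162 × (1 − loss).

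| Loss | Analysed per arm | One-sided 0.05 | Two-sided 0.05 |
|---|---|---|---|
| 0% | 162 | 87.2% | 79.4% |
| 5% | 153.9 | 85.7% | 77.3% |
| 10% | 145.8 | 84.0% | 75.0% |
| 15% | 137.7 | 82.1% | 72.6% |
| 20% | 129.6 | 80.0% | 70.0% |

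Exact binomial enumeration of the uncorrected chi-square test gives, two-sided, 80.8% at 162 and 71.2% at 130 per arm. One-sided, it gives 88.4% and 81.4%.

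**4. An alternative origin for 162**

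The unpooled two-sided formula gives 161.8 per arm with no loss allowance. That matches 162 too, but the text says the calculation is one-tailed and mentions loss, so the one-sided route in step 1 is the one the document describes.

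**The case against.** The strongest defence has four parts.

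- **The stated calculation is correct and openly one-sided.** This stands. The only level given for a test anywhere is one-sided 0.05, and a chi-square with one degree of freedom can serve such a test by checking the direction and using the signed root. The Statistical approach section never writes that the test is two-sided; that is the ordinary reading of the named test, not a statement of the plan. What remains is that the section does not say the directional version is meant, so the sections do not settle the rule between them.

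- **A reader might infer that the plan simply has 70% power.** The document does not support that. The 20% is a ceiling, the FAS with LOCF may analyse close to 162 per arm, and the endpoint is at week 4 of a 24-week treatment period, so loss by then may be smaller. With all 162 analysed, two-sided power is essentially on target. Two limits apply. The PPS would normally exclude incomplete patients. Also, week 4 is the first post-baseline visit, so a patient who misses it has only a baseline score to carry forward and shows no improvement. As an illustrative assumption, if 20% of each arm were counted as non-responders for this reason, the rates would be 0.8 × 83% = 66.4% and 0.8 × 93% = 74.4%, and two-sided power at 162 per arm would be about 35%. Keeping everyone in the analysis therefore does not by itself secure 79%.

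- **A reader might infer a conflict with the 95% interval as well.** The sentence "The RR and 95% confidence interval of the two groups were calculated by logistic regression model" directly follows the definition of a cardiovascular event and most naturally belongs to that analysis. No interval is stated for the angina response, so it cannot be said that its test and interval might disagree. The point rests on the chi-square test alone.

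- **Sidedness is a detail for an analysis plan that is not shown.** This would hold if the article were silent. It states a level and direction in one section and a test in another, and those two statements need to agree.

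**Conclusion.** The point holds as a mismatch between the stated power and the stated analysis, not as an arithmetic error. The 80% with a 20% loss allowance is true of a one-sided 0.05 test only. If the chi-square test is read in its usual two-sided form at 5%, power is about 79% (exact 81%) with no loss, about 75% at 10% loss and about 70% (exact 71%) at the ceiling. The shortfall is thus between roughly nothing and 10 percentage points.

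These figures assume the plan's 83% and 93% rates among the patients analysed, equal loss in both arms and no continuity correction. The two-sided 5% level is an inference from the named test.

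**What to change.** Before unblinding, state one sidedness and one level for the angina-response test, in the same words in the Sample size and Statistical approach sections. There are two acceptable routes:

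1. **Two-sided 0.05.** Keep the chi-square test, call it two-sided, and restate power at 83% versus 93% as about 79% with no loss, 75% at 10% and 70% at 20%.
2. **One-sided 0.05.** Keep the 80% figure, name a directional test in the Statistical approach section (for example the signed root of the chi-square against 1.645), report the matching one-sided 95% bound (the lower limit of a 90% interval), and say plainly that the false-positive rate for a benefit claim is 5%.

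Under either route, report separately that the one-sided calculation needs 130 evaluable per arm and that 162 per arm are randomised to allow for 20% loss.

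The cost is wording, with ethics committee re-approval as the protocol requires for amendments. Route 1 makes the stated power less favourable; route 2 makes the 5% error rate explicit. Neither asks for more patients.

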### Statistical approach

Efficacy will be determined by the full analysis set (FAS) and per protocol set (PPS), while the safety assessment will be based on the safety set (SS). The statistical evaluation of FAS will follow the principle of intention to treat (ITT). For the missing values of the main efficacy evaluation indicators, the method of the last observation carried forward (LOCF) will be used. Continuous variables were shown as mean ± standard deviation (SD) and were compared using the *t* test or the nonpara-metric Mann-Whitney *U* test, as appropriate. The count variables were shown as the number of cases and percentage, and the chi-square test was used for comparative analysis. The symptom improvement rate of angina is to calculate the total score of angina pectoris according to the degree of pain, the number of attacks, and the duration. The total score is effective when it is lower than or equal to 30% of the baseline, and invalid when it is less than 30%. The symptom improvement rate of angina was analyzed by chi-square test. The participants who had any cardiovascular event during 24 weeks of treatment will be identified as the occurrence of cardiovascular events. The RR and 95% confidence interval of the two groups were calculated by logistic regression model. Statistical analysis will be performed using SAS 9.4 software.

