### Study design

The study is designed as a randomized, double-blind, multicenter, placebo-controlled trial. To avoid regional differences, the study will be conducted in 11 hospitals from different regions of China. Data management and statistical analysis will be performed by the statistical department in China Evidence-based Medicine Center, West China Hospital, Sichuan University. This study will be conducted by following the Declaration of Helsinki and the guidelines of Good Clinical Practice (GCP). The study has also been approved by the ethics committee in Shuguang Hospital (Ethics approval number: 2019-649-04-01). Trial registration: ChiCTR, ChiCTR1800014258. Registered on 13 March 2019 at chictr.org.cn (http://www.chictr.org.cn/showproj.aspx?proj=34955). Before randomization, all participants in this study must sign an informed consent form.

The participants who fulfill both the inclusion and exclusion criteria will be recruited into the study. Participants sign consent form. Demographic information (including date of birth, gender, ethnicity, height, and weight), medical and treatment history (including course of disease, smoking, drinking history), angina pectoris score, Seattle angina pectoris scale score, physical and chemical examinations (EKG, blood lipids, C-reactive protein, tumor necrosis factor alpha, and interleukin 6) and scores from the four traditional Chinese medicine (TCM) diagnostic methods are collected. The study design is shown in Fig. 1.

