### Randomization

Eligible patients will be randomly assigned to the treatment group or the control group in a 1:1 ratio, using SAS 9.4 statistical software and a block randomization schedule. The size of the blocks is four. Randomization of the trial participants will be completed in an independent data center. Each participating hospital will have an independent drug administrator responsible for random coding and drug management. Each center set up an independent drug administrator, who was responsible for random coding and drug management.

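### Symptom response and continuous outcomes are fixed as unadjusted two-sample tests although baseline scores are collected at 11 hospitals; the tests are valid, but precision is lost, mainly for continuous secondary outcomes

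*Protocol article*

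**What the plan says.** The Statistical approach section assigns continuous variables to a t test or a Mann-Whitney U test. For categorical data it says: "The count variables were shown as the number of cases and percentage, and the chi-square test was used for comparative analysis". It then names the chi-square test again for the symptom improvement rate of angina, one of the two primary outcomes. Cardiovascular events, the other, are to be analysed by a logistic regression model whose covariates are not given.

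Under Study design, "the study will be conducted in 11 hospitals from different regions of China", and the data collected before treatment include "angina pectoris score, Seattle angina pectoris scale score, physical and chemical examinations". CCS grade is not in that list but is known at entry, because grades I to III are an inclusion criterion. The Randomization section gives 1:1 allocation in blocks of four and adds: "Each participating hospital will have an independent drug administrator responsible for random coding and drug management". It does not say whether the blocks are formed separately within each hospital. The Discussion says the combined data from all centres will be analysed. No centre factor is named anywhere.

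**The concern.** A chi-square, t or Mann-Whitney test compares two samples and has no place for a covariate. Naming these tests therefore settles that the baseline value and hospital are not used in those comparisons. This is a stated method, not a detail left open.

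The baseline value of a repeatedly measured score usually carries information about its later value, and hospitals in different regions may differ in case mix and scoring. Leaving both out of the analysis discards precision that the trial has already paid to collect. At stake are the width of the intervals and the chance of detecting a real effect. The validity of a positive result is not at stake.

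**Working it through.** **1. The plan's own sample size.** The Sample size section says "the effective treatment rate for patients receiving standard western medicine treatment is 83"% and that the rate "for patients receiving both traditional Chinese medicine and western medicine treatment is 93"%. It adds "significance level α is 0.05 and power (1-β) is 0.80 in the one-sided test", 1:1 allocation and an incomplete rate below 20%. With pooled variance and no continuity correction:

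- n = [1.645·√(2·0.88·0.12) + 0.842·√(0.83·0.17 + 0.93·0.07)]² / 0.10² ≈ 129.5, or 130 per group.
- Allowing for 20% incomplete: 129.5/0.8 = 161.9, or 162 (130/0.8 = 162.5, or 163 if rounded up first).

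The stated 162 per group is reproduced. It comes from an unadjusted two-proportion comparison, so the planned power does not rely on adjustment. Formula power at 162 per group is 0.87 one-sided and 0.79 two-sided. At 130 per group it is 0.80 and 0.70.

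**2. Continuous outcomes.** The protocol article gives no baseline/follow-up correlation r, so 0.3 to 0.7 is assumed, with equal variances at the two times. It does not say whether the t test is on follow-up scores or on changes, so both are shown.

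- ANCOVA variance relative to a follow-up t test: 1 − r².
- ANCOVA variance relative to a change-score t test: (1 − r²)/[2(1 − r)] = (1 + r)/2.

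| r (assumed) | 1 − r² | cut vs follow-up t test | (1 + r)/2 | cut vs change t test |
|---|---|---|---|---|
| 0.3 | 0.91 | 9% | 0.65 | 35% |
| 0.5 | 0.75 | 25% | 0.75 | 25% |
| 0.7 | 0.51 | 49% | 0.85 | 15% |

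ANCOVA is more precise than either t test throughout the range. At r = 0.5 the gain is worth 324/0.75 = 432 patients analysed without adjustment. A follow-up comparison with 80% power (two-sided 0.05) would rise to about 84%, 90% and 98% at r = 0.3, 0.5 and 0.7.

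**3. Symptom response.** The protocol article gives no between-hospital variance, so SDs of 0 to 1.0 on the logit scale are assumed. Trials were simulated with 162 per group, 11 hospitals, allocation balanced within hospital and marginal rates of 83% and 93%. There were 1,000 runs per setting, with Monte Carlo error of about 1 point.

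- Power, CMH test by hospital minus plain chi-square test: about 0 to +3 points. The largest difference was 79.2% to 82.2%, two-sided, at SD 1.0.
- Power, logistic model with one baseline covariate (log-odds 0 to 1.0 per SD) minus chi-square: about −1 to +4 points.
- Type I error of the plain chi-square, one-sided nominal 5% (3,000 runs per setting): 4.9% with hospital SD and covariate effect both 0.5, and 4.5% with both 1.0.

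A two-sided run of 20,000 replicates with allocation balanced within hospital gave these type I errors:

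- SD 0.5: chi-square 4.5%, CMH 4.9%.
- SD 1.0: chi-square 3.8%, CMH 5.0%.

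With blocks not formed within hospital, the two-sided chi-square error was 4.5% and 5.0% at SD 0.5 and 1.0, so the conservatism at SD 1.0 disappears.

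**4. Room for model terms.** Expected non-responders are 162·0.17 + 162·0.07 = 27.5 + 11.3 ≈ 39. A logistic model with 10 hospital contrasts, treatment and baseline score has 12 coefficients besides the intercept: 39/12 ≈ 3 non-responders per coefficient.

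**The case against.** The strongest defence is that unadjusted tests are valid in a randomised trial, that the sample size was derived for such a test, and that covariate terms are often left to an analysis plan, which is not shown here. The first two points stand, and they keep this a matter of efficiency. The third does not meet the case: the tests named cannot carry covariates, so an analysis plan that added them would depart from the published text.

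It is also fair to say that the larger gains concern secondary outcomes on which the trial was not sized, that they rest on assumed correlations, and that the symptom response is already defined relative to baseline. All of this stands and limits the weight of the point.

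Four stronger readings are tempting but not supported:

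- **Every comparison in the trial is unadjusted.** The logistic model for cardiovascular events has covariates neither stated nor excluded, and it is not part of this point.
- **The 5% level of the chi-square test is wrong.** The test is mildly conservative only if allocation is balanced within hospital. The Randomization section does not state this, and nothing suggests inflation.
- **The primary outcome loses substantial power.** A gain of up to about 5 points (80–81% to 85%) appeared only at an assumed hospital SD of 1.5, for which the protocol article gives no basis.
- **CCS class and EKG efficacy will be tested by chi-square, ignoring order.** The text does not say which rule applies to them; a rank test is also available under it, and EKG categories are not defined.

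**Conclusion.** The point holds as a loss of precision, not as an error of validity. It matters most for continuous secondary outcomes: a variance reduction of 9% to 49% against follow-up scores, or 15% to 35% against changes, is forgone if r lies between 0.3 and 0.7. For the primary symptom response the expected gain from stratifying by hospital is small, about 0 to 3 points of power, and depends on an assumed hospital SD of up to 1.0 and on allocation balanced within hospital. If hospitals differ little, or the blocks were not formed within hospital, the gain may vanish or become a slight loss. The change is worth making for the continuous outcomes and a modest refinement for the primary.

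**What to change.** Before unblinding, amend the analysis text as follows:

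- **Continuous outcomes:** ANCOVA of the value at each visit, with the baseline value of the same measure and hospital as covariates, pooling small hospitals by a rule set in advance.
- **Symptom response:** CMH test with a common risk difference, stratified by hospital with small hospitals pooled. Avoid a logistic model with separate terms for all 11 hospitals, given about 39 expected non-responders.
- **CCS class, if analysed as ordered grades:** an ordinal model or rank test that includes baseline class.
- **Randomization:** state whether blocks were formed within hospital, since this determines how the plain chi-square test behaves.

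The baseline angina and Seattle scores, entry CCS grade and hospital are already recorded. The cost is analysis wording and programming only, with no change to data collection or sample size.

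### The week-4 angina score is tested only as a responder rate; a prespecified baseline-adjusted analysis of the full score would recover discarded information at almost no cost

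*Protocol article*

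**What the plan says.** All references are to the protocol article.

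- **Outcome.** The Abstract makes the symptom improvement rate from baseline to 4 weeks one of two primary outcomes; the other is cardiovascular events.
- **Score.** Statistical approach says the improvement rate is obtained by a rule to "calculate the total score of angina pectoris according to the degree of pain, the number of attacks, and the duration".
- **Cut.** The next sentence reads "The total score is effective when it is lower than or equal to 30% of the baseline, and invalid when it is less than 30" (per cent).
- **Test.** "The symptom improvement rate of angina was analyzed by chi-square test". No other test is tied to this score. The same section has a general rule that continuous variables "were compared using the *t* test or the nonpara-metric Mann-Whitney *U* test, as appropriate", without naming the angina score.
- **Planning rates.** Sample size assumes "the effective treatment rate for patients receiving standard western medicine treatment is 83" (per cent) and that the rate "for patients receiving both traditional Chinese medicine and western medicine treatment is 93" (per cent), with "significance level α is 0.05 and power (1-β) is 0.80 in the one-sided test", 162 per group and an incomplete rate below 20%.
- **Data.** Study design lists an angina pectoris score among the items collected at baseline.

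**The concern.** A three-component score with a baseline value carries graded information on how much each patient's angina changed. The stated test keeps only the side of a line on which each patient falls. With 83% of controls expected to be effective, the line lies well into the tail of the improvement distribution. A patient just past it and a patient free of angina count the same, and only about 17% of controls have room to register a benefit.

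Two things are at stake. A real effect on angina burden could be missed although the data to show it are in hand. And a responder rate alone cannot say by how much angina was reduced.

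**Working it through.** **Inputs.** From Sample size: 83% and 93%, one-sided α 0.05, power 0.80, 162 per arm, incomplete rate up to 20%. I take the effective treatment rate there to be the symptom responder rate. Assumed, because the article gives no mean, SD or distribution for the score: normal improvement, equal SDs in both arms, one common shift.

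**1. The plan's own figure.** With pooled variance under the null, p̄ = 0.88:

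n = [1.645·√(2·0.88·0.12) + 0.842·√(0.83·0.17 + 0.93·0.07)]² / 0.10² = (0.756 + 0.382)² / 0.01 ≈ 130 per arm.

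Allowing for 20% incomplete, 130/0.80 = 162.5, or 163, against 162 stated. The figure reproduces, so the planned 80% power belongs to the binary rate.

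**2. Shift implied on the full scale.** d = z(0.93) − z(0.83) = 1.476 − 0.954 = 0.522 SD.

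**3. Power.** The cut has power Φ{[0.10·√n − z_α·0.4596]/0.4541}, where 0.4596 = √0.2112 and 0.4541 = √0.2062. The full scale has power Φ(d·√(n/2) − z_α). I use n = 130 (162 less 20%) and n = 162 (everyone kept, as last observation carried forward could do in the full analysis set). Both sidednesses are shown because Sample size is one-sided and Statistical approach does not say which applies.

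| n per arm | α 0.05 | Cut | Full scale | Gain, points |
|---|---|---|---|---|
| 130 | one-sided | 80.1% | 99.5% | 19.4 |
| 130 | two-sided | 70.1% | 98.8% | 28.7 |
| 162 | one-sided | 87.3% | 99.9% | 12.6 |
| 162 | two-sided | 79.4% | 99.7% | 20.3 |

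**4. Departures from the model** (130 per arm, one-sided; simulated with 3,000 runs, except the reduced-shift case).

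- 40% of controls at complete relief: full scale 97% (t test) to 98% (rank test), a gain of about 17 to 18 points.
- 60% at complete relief: 93% to 95%, a gain of about 13 to 15 points.
- Shift over the full scale only 60% of that implied (0.6 × 0.522 = 0.313 SD): about 81%, level with the cut.
- Treatment only moves patients across the cut, with no shift elsewhere: full scale 41% (rank test) to 46% (t test), against 80% for the cut.

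**5. Why baseline adjustment matters.** The 0.522 SD is a shift in improvement from baseline. A test of the raw week-4 score also carries the spread of baseline severity. On a log scale, with baseline independent of the change and baseline SD equal to k times the SD of change, the usable shift is 0.522/√(1 + k²). At 130 per arm, one-sided:

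- k = 1: 0.369 SD, power about 91%
- k = 1.33: 0.313 SD, about 81%, level with the cut
- k = 2: 0.233 SD, about 59%, well below the cut

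**6. The cut as printed.** If both percentages are the score as a share of baseline, a score below 30% of baseline is both effective and invalid, and a score above 30% has no class. If one percentage means a reduction from baseline, the sentence does not say which.

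**The case against.** The strongest reply is that this is a choice between two legitimate endpoints. The responder rate is prespecified, easy to read and correctly sized. That stands: a reader might infer that the cut leaves the trial underpowered, but 162 per arm was computed for the binary rate and reproduces to within one patient. The loss is only relative to another analysis of the same data.

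A reader might also take the 19 points as following from 83% versus 93% alone. They do not. Two proportions fix no mean, SD or shape, and the figure needs the normal common-shift model. Where treatment acts only at the cut, the ranking reverses.

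It is tempting to replace the primary test with the Mann-Whitney test the plan already names. Neither part is supported. Unadjusted, that test of the week-4 score can do worse than the cut when baseline severity varies widely. Replacing the formal primary would detach it from the only sample-size basis given, with 293 of 324 already recruited (Trial status) and ethics reapproval required for any protocol change (Data management and quality control).

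Finally, the silence about supporting analyses and about a source for the cut proves little. Supporting analyses are commonly left to the analysis plan, which is not shown, and an article condenses its sources. The angina class, Seattle score and emergency-drug use also give graded information on angina burden. What remains is that the article ties the score only to a chi-square test of the cut, and that a better use of the same data is cheap.

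**Conclusion.** The point holds as a cheap improvement, not as an error in the sample size or a reason to change the primary test. The graded score is reduced to a yes/no, and only that is named for testing. Under a normal, equal-SD, common-shift model, a full-scale analysis of improvement would have about 99% power against 80% for the cut at 130 per arm, one-sided 5%. The gain is about 13 to 29 points over the n and sidedness examined. It shrinks with heavy ties at complete relief and vanishes if the effect is confined to the cut. The documents contain nothing that settles which shape applies.

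The contradiction in the effective/invalid sentence needs none of these assumptions. It must be resolved whatever is decided about the supporting analysis, because the formal primary test depends on it.

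**What to change.** 1. Keep the responder rate and its chi-square test as the formal analysis of the week-4 symptom primary.
2. Before unblinding, add to Statistical approach or the analysis plan, as the first supporting analysis of the same outcome, a full-scale baseline-adjusted comparison of the week-4 total angina score. Use either a linear model with the baseline score as covariate or a rank test on change relative to baseline. Name one, and report the estimated between-arm difference with a 95% confidence interval.
3. Do not use an unadjusted Mann-Whitney test of the week-4 score for this purpose.
4. Reconcile the effective/invalid sentence so that every score falls into exactly one class, stating whether each percentage is a share of baseline or a reduction from it.

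**Cost.** Wording, plus ethics reapproval if it goes in as a protocol change. No new data, visits or patients are needed, and the sample-size basis is untouched. The downside is one more analysis to report, whose result reads less directly than a responder percentage.
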